### The Waitlist

Participants in the Waitlist undergo the same set of assessments (minus those that tap into working alliance), under the same schedule as the active groups, after which time they will be given the possibility to join in-person group sessions.

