#### Assignment to interventions

The participants are randomly assigned to one of the three conditions (Metaverse, In-Person, Waitlist) using a sequence generated by the software randomizer.org.

The process of random allocation is executed by the project manager employing a straightforward random sequence, assigning one of three distinct numbers to each participant—either 1, 2, or 3, based on the number of the experimental condition.

Participants are enrolled by the project manager and trained facilitators from partner NGOs, with eligibility confirmed through thorough screening assessments. The project manager independently assigns participants to intervention groups, and allocation concealment is maintained by storing allocation lists as password-protected documents, accessible only after baseline assessments, ensuring that both participants and recruiters remain blind to group assignments until the intervention begins.

The Metaverse and In-Person groups are facilitated by two different psychotherapists, trained in evidence-based psychotherapies and group interventions, and who have at least 1 year of experience working with refugees. Both psychotherapists follow the same protocol structure (described in the “Interventions” section) to deliver the intervention.

The principal investigator and the statisticians conducting the data analysis remain unaware of the experimental condition until the study concludes.

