The improvement in the mental health and well-being scores within and between the groups will be examined using mixed-effects linear regression with a random intercept and slope over time (three assessments: baseline, after session 2, and post-treatment) and fixed effects for treatment assignment. The 3-month follow-up data will be analyzed using linear mixed effects model that incorporates random intercepts for participants and facilitators. Additionally, we may consider including random slopes for time if the data structure warrants it. If ICC analyses will indicate the presence of a hierarchical structure, we will proceed with conducting multilevel analyses. In addition, we will incorporate fixed effects for time and intervention condition and include any necessary covariates. We intend to perform longitudinal analyses in order to ascertain the long-term effects of the intervention. To evaluate changes in outcome measures from the initial measurement to each subsequent assessment, we plan to employ repeated measures ANOVA, where the data is complete, or mixed effects models, where data is incomplete. Moreover, we acknowledge that the linear mixed-effects model allows for the inclusion of covariates (we plan to control for demographics), and this flexibility makes it a robust alternative to repeated measures ANOVA, especially in complex datasets. The use of covariates was taken into account appropriately in the mixed-effects model, which is another reason we plan this approach when dealing with missing or incomplete data. The results of the other measures—demographic variables and therapeutic alliance as potential moderators and mediators—will be examined in an exploratory manner, utilizing regression models or mediation analyses. The error probability and the issue of multiple testing will be addressed either by employing the Bonferroni correction or the false discovery rate correction. Missing data—over 5%—will be handled with multiple imputation methods. Oversight and monitoring of the data collection process is conducted by the principal investigator and the project manager. Check-in regular meetings are held to review the progress of data collection, address any issues that may arise, and ensure compliance with the study protocol and ethical guidelines.

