### Access to data statement

The principal investigator has direct access to the dataset, and the data dispersed to project team members will be blinded to any identifying information.

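### The stated blinding of the principal investigator and statisticians conflicts with the data structure and access the article describes, which leave the waitlist arm identifiable

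*Protocol article*

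**What the plan says.** The blinding claim is in the protocol article, Assignment to interventions: "The principal investigator and the statisticians conducting the data analysis remain unaware of the experimental condition until the study concludes". Other parts of the article bear on it:

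- **The Waitlist, on assessments:** "Participants in the Waitlist undergo the same set of assessments (minus those that tap into working alliance), under the same schedule as the active groups".
- **Data collection, management, analysis, on alliance:** "demographic variables and therapeutic alliance as potential moderators and mediators—will be examined in an exploratory manner".
- **Same section, on facilitators:** "The 3-month follow-up data will be analyzed using linear mixed effects model that incorporates random intercepts for participants and facilitators". It adds that multilevel analyses will follow if intraclass correlations point to a hierarchical structure.
- **Assignment to interventions, on staffing:** "The Metaverse and In-Person groups are facilitated by two different psychotherapists". The project manager executes the allocation, using the codes 1, 2 and 3 according to the number of the condition. Allocation lists are password-protected and open only after baseline.
- **Access to data statement:** "The principal investigator has direct access to the dataset". Data passed to other team members are stripped of identifying information; nothing is said about arm.
- **Oversight and training:** the investigator and the project manager jointly oversee data collection (Data collection, management, analysis) and train the facilitators (Monitoring study implementation). The Discussion says that neither takes part in sessions.

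**The concern.** A blind depends on what the people concerned can see. Here the article states that two roles are blind, and elsewhere describes data and access that would show at least one of them who is on the waitlist.

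This matters because little other masking exists. PHQ-9 and GAD-7 are self-reported, participants and recruiters are described as blind only until the intervention begins, and the Discussion concedes that psychotherapists cannot be blinded. Masking of the investigator and analysts is the only blind claimed after that point. It would also protect the choices left open in Data collection, management, analysis: random slopes, which covariates, Bonferroni or false discovery rate, multilevel or not. The waitlist is the reference arm for asking whether improvement exceeds the passage of time (Objectives). Whoever can identify it can see the direction of both active-versus-waitlist contrasts while those choices are still open, and the publication would report them as made blind.

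**Working it through.** **1. Denominator.** The only related figure is the total of 45 under Sample size. Stated inputs: f = 0.25, alpha = 0.05, power 0.95, k = 3 groups, m = 4 measurements. Assumed, because not stated: correlation 0.5 between repeated measures and no sphericity correction.

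- Noncentrality = f² × N × m / (1 − correlation) = 0.0625 × 45 × 4 / 0.5 = 22.5
- df1 = (3 − 1)(4 − 1) = 6; df2 = (45 − 3)(4 − 1) = 126
- Power at N = 45 is 0.955. The smallest N reaching 0.95 is 44, or 45 for equal arms.

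The figure reproduces. It says nothing about blinding and serves only to size the arms: 45 / 3 = 15 each, so 45 − 15 = 30 active, if the arms are equal.

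**2. What each field shows.**

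| Field | Waitlist | Active arms | What its holder learns |
|---|---|---|---|
| Working-alliance items | Absent by design | Collected | Who is on the waitlist |
| Facilitator or group | None while assessed | Present | Who is on the waitlist; probably also a split of the active participants |

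Three masked arms can be labelled in 3! = 6 ways. Once the waitlist is known, 2! = 2 ways remain. A facilitator code masked as A/B splits the active participants into two sets, if each format has one psychotherapist, but does not say which set is Metaverse, so 2 ways still remain. An unmasked facilitator name could settle it for someone who trained the psychotherapists.

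**3. Which analyses need these fields.** Alliance is exploratory. The facilitator intercept ("random intercepts for participants and facilitators") is stated for the 3-month model only. The model for the first three assessments names a random intercept and slope over time and fixed effects for treatment, with no facilitator term. The primary outcomes, change from baseline to post-intervention, can therefore be modelled without either field. The exception is the intraclass-correlation step, which needs a cluster identifier and is not tied to one model.

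**4. Who holds the data.** The investigator has direct access, with no date and no restriction on fields, and shares oversight with the person who knows every assignment. The stripping described for other team members removes identity, not arm.

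**5. Arm code.** Waitlist is number 3 in the Abstract, in Trial design and in Participant timeline, whereas Metaverse and In-Person swap numbers 1 and 2 between those lists. The article does not say that analysts receive this code. If they did, it would mark the waitlist directly.

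**The case against.** The strongest reply is that the article condenses a longer protocol, and that file preparation and staged release are commonly left to it. That stands against any complaint that a masking procedure is merely undescribed. It does not remove the conflict between a stated blind and a stated data structure and access rule.

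A reader might go further and infer that the blind is impossible, that all 45 participants are unblinded, or that this happens at the first data export. The documents do not support any of these:

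- A masked facilitator code does not label the two active sets, and one psychotherapist per format is itself an inference from "The Metaverse and In-Person groups are facilitated by two different psychotherapists".
- Neither alliance nor facilitator is a stated term in the baseline-to-post model, so a file without them could serve the primary outcomes.
- No section dates a data release, and none says that the dataset open to the investigator carries the allocation. The allocation lists are protected separately.
- Training facilitators does not disclose any participant's arm, and keeping the investigator out of sessions is a real, if partial, safeguard. Harms are handled by a separate supervising psychologist.

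The claim is also limited in time. If the statisticians receive data only after the study concludes, it could be literally true for them. It would then give no protection to modelling choices made after release, and it would not answer the investigator's undated access or oversight role during collection.

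**Conclusion.** The point holds for waitlist versus active condition. As described, the waitlist (about 15 of 45) is recognisable to anyone holding the full item-level file, and the investigator's access and shared oversight sit badly with the claim. For Metaverse versus In-Person, the documents show at most a split of the remaining 30 or so into two sets, which stay unlabelled if facilitator codes are masked.

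This rests on three assumptions: roughly equal arms, one psychotherapist per format (for the split only), and alliance or facilitator fields being present in the file that the investigator or analysts hold while still meant to be blind. The documents do not show that anyone has been unblinded. The correction is worth making because it is cheap and protects analysis choices that are still open.

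**What to change.** 1. Have the project manager, who already knows the allocation, issue a masked analysis file containing IDs, visit, outcome scores, baseline covariates and a scrambled arm code. Hold back alliance, facilitator, group and attendance fields.
2. Withhold the full dataset from the investigator and the statisticians until covariates, random slopes and the multiplicity correction are fixed and dated. Amend Assignment to interventions and the Access to data statement to say so.
3. Do not use the masked file to settle the clustering question, since an intraclass correlation needs the cluster fields. Either prespecify the clustering structure without reference to that result, or decide it after the other choices are locked.
4. If this is not feasible, restrict the claim in Assignment to interventions to say that the investigator and analysts were not blind to waitlist versus active condition.

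The cost is a second export file, edits to two sections, and a short delay before alliance and clustering terms can be fitted.

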#### Data collection, management, analysis

Eligible participants are assigned a unique identification number and asked to complete the assessment package (primary, secondary, and other outcomes, as well as demographics). The same set of measures are administered mid-intervention (after session 2), final intervention (after session 5), and 3 months after the final session (follow-up assessment).

To ensure high accuracy of data collection, all the measures are completed electronically, via an established survey solution such as QuestionPro, to minimize the risk of missing responses or errors in data entry. The facilitators are responsible for assisting the participants in this process, providing clarifications and explanations when needed.

To promote participant retention and follow-up completion, several strategies are being used. First, the participants receive a clear and complete description of the project, including, but not limited to, information regarding the goals of the support groups, their efficacy, and long-term effects based on evidence. Additionally, the participants will receive reminders about the upcoming session by email or other means to encourage the continuation of the program.

The improvement in the mental health and well-being scores within and between the groups will be examined using mixed-effects linear regression with a random intercept and slope over time (three assessments: baseline, after session 2, and post-treatment) and fixed effects for treatment assignment. The 3-month follow-up data will be analyzed using linear mixed effects model that incorporates random intercepts for participants and facilitators. Additionally, we may consider including random slopes for time if the data structure warrants it. If ICC analyses will indicate the presence of a hierarchical structure, we will proceed with conducting multilevel analyses. In addition, we will incorporate fixed effects for time and intervention condition and include any necessary covariates. We intend to perform longitudinal analyses in order to ascertain the long-term effects of the intervention. To evaluate changes in outcome measures from the initial measurement to each subsequent assessment, we plan to employ repeated measures ANOVA, where the data is complete, or mixed effects models, where data is incomplete. Moreover, we acknowledge that the linear mixed-effects model allows for the inclusion of covariates (we plan to control for demographics), and this flexibility makes it a robust alternative to repeated measures ANOVA, especially in complex datasets. The use of covariates was taken into account appropriately in the mixed-effects model, which is another reason we plan this approach when dealing with missing or incomplete data. The results of the other measures—demographic variables and therapeutic alliance as potential moderators and mediators—will be examined in an exploratory manner, utilizing regression models or mediation analyses. The error probability and the issue of multiple testing will be addressed either by employing the Bonferroni correction or the false discovery rate correction. Missing data—over 5%—will be handled with multiple imputation methods. Oversight and monitoring of the data collection process is conducted by the principal investigator and the project manager. Check-in regular meetings are held to review the progress of data collection, address any issues that may arise, and ensure compliance with the study protocol and ethical guidelines.

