### Interventions

Our research team designed the intervention protocol following evidence-based practices for support groups, specifically drawing from Cognitive Behavioral Therapy (CBT) principles [26]. Additionally, the protocol is based on guidelines from the United Nations High Commissioner for Refugees [27], Inter-Agency Standing Committee (IASC, 2007), the World Health Organization [28], and the Finish Refugee Council for support groups working with refugees [29]. Our intervention adopts a trauma-informed approach, acknowledging the unique and complex needs and experiences of individuals who have been exposed to traumatic events. The language used for the intervention sessions is Russian. This decision was made in consultation with previous Ukrainian refugees that the team worked with, as it is the preferred and most used language among this community. This language choice was deliberate to enhance inclusivity, allowing us to enroll a broader range of participants who could benefit from the intervention. To ensure agreement and comfort with the language choice, we included a question tapping into this, at the beginning of the screening process. We have observed no dropouts due to language concerns so far, supporting the argument for the effectiveness of our language inclusivity approach.

Both the Metaverse and In-Person conditions undergo a 1.5-h session each week for 5 weeks. Licensed psychotherapists facilitate both intervention conditions and follow the same protocol structure, which aims to improve the mental health and well-being of Ukrainian refugees and deliver psychoeducation on mental health and gender-based violence.

For both intervention conditions, the program has the following structure: (1) intake and the baseline assessments (described below) are conducted, (2) sessions 1 and 2, (3) mid-program assessment, (4) sessions 3, 4, and 5, (5) final assessment, (6) 3-month follow-up.

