#### Other measures

*Demographics* are collected through questions related to age, sex, gender, place of birth, country of displacement, assistance received while in the host country, marital status, and educational level. Questions regarding whether a family member died in the war, or the timeframe of arrival in the host country are also addressed. In the demographic section, questions concerning previous/actual involvement in therapeutic interventions and previous/actual mental disorders are also included.

The *Working Alliance Inventory – Short Form* (WAI-SR; [35]) was modified and is used to assess the therapeutic alliance within intervention groups. The measure is a 5-point Likert (1—Seldom; 5—Always) instrument consisting of 12 statements related to the relationships between client and therapist. For the present study, 6 items were adapted and are used to assess the alliance between support group facilitators and participants. These items pertain to the agreement on goals (e.g., “My support group leader and I agree on what is important for me to work on”), agreement on tasks (e.g., “My support group leader helps me to do what’s necessary to improve my situation”), and bond (e.g., “I feel comfortable working with my support group leader”), with each subdomain consisting of 2 questions.

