**Fig. 2 Fig2:**
[figure not shown]
CONSORT flow diagram [36] showing subject allocation to the intervention conditions

The study’s assessment and session timings are as follows: The baseline assessment session is delivered at enrollment, serving as the initial evaluation point. Between the baseline and the first session, approximately 1 to 2 weeks elapse. Subsequent sessions are held weekly thereafter. The mid-intervention assessment occurs after the second session but before the third, either on the day of the third session or 1 day prior. Similarly, the final assessment takes place after the fifth session, either on the same day or 1 day after. Additionally, a follow-up assessment is conducted 3 months after the conclusion of the intervention. In-person sessions are held at one of the NGO collaborators’ offices, providing a conducive environment for participant engagement and support.

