There are, nonetheless, several limitations that must be acknowledged. First, as with many clinical trials testing psychological interventions, psychotherapist blinding is not possible. To minimize possible biases, the principal investigator and the project manager are not involved in any support group sessions. Second, the efficacy of virtual support groups may be influenced by the availability and accessibility of technology (e.g., familiarity with virtual platforms, access to a stable internet connection, etc.). To minimize the risk, participants receive technical assistance through the study and a short introduction on how to use the platform is in place. Third, virtual interventions might face higher rates of attrition and dropout compared to in-person. We monitor and report attrition rates and will conduct sensitivity analyses to assess the impact of dropouts on the results. Nevertheless, we acknowledge that, while Metaverse anonymity comes with several benefits, it can have some limitations for some people (e.g., participants not feeling comfortable not knowing who they are speaking to, maintaining confidentiality, whether the team can know for sure who is accessing the Metaverse platform). To minimize the risks, we have implemented several measures to ensure participant comfort and confidentiality within the Metaverse platform. Firstly, participants have the opportunity to meet the trainer before the sessions, either online or in-person, providing them with the opportunity to establish a rapport and familiarize themselves with the facilitator. Secondly, to ensure that the team can verify the identity of participants accessing the Metaverse platform, each participant is given a unique access code. This code is exclusively available to the participant and serves as a secure identifier when accessing the platform. By providing participants with individualized access codes, we can accurately track and monitor participation while maintaining confidentiality and ensuring that only registered participants have access to the sessions.

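### Facilitators help participants complete the self-report outcomes, and participants are told of the groups' efficacy; both can bias unblinded PHQ-9 and GAD-7 scores against the waitlist

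*Protocol article*

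**What the plan says.** All measures are completed electronically at baseline, mid-intervention, post-intervention and follow-up. For that process the protocol article (Data collection, management, analysis) states: "The facilitators are responsible for assisting the participants in this process, providing clarifications and explanations when needed". It sets no script and no limit on the help.

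The same section continues: "To promote participant retention and follow-up completion, several strategies are being used". The first of these is a project description that includes "information regarding the goals of the support groups, their efficacy, and long-term effects based on evidence".

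Other relevant statements in the article:
- **Interventions:** "Licensed psychotherapists facilitate both intervention conditions".
- **Assignment to interventions:** "Participants are enrolled by the project manager and trained facilitators from partner NGOs". Participants and recruiters are blind only until the intervention starts. After that, only the principal investigator and the statisticians are kept unaware of condition.
- **Participant timeline (text after Fig. 2):** "the final assessment takes place after the fifth session, either on the same day or 1 day after".
- **Other measures:** the adapted alliance inventory includes "I feel comfortable working with my support group leader".
- **The Waitlist:** the same assessments on the same schedule, without the alliance measure.
- **Discussion:** "psychotherapist blinding is not possible". The stated mitigation is that the principal investigator and project manager stay out of the sessions.

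**The concern.** Both primary outcomes are rated by participants who know their arm. If the person who ran the group also explains the questions, right after the last session and in a package that rates that same person, answers may lean towards reporting improvement. A waitlist participant has no group leader to please. Telling participants that the groups work adds an expectation. The message may be the same for everyone, but it acts differently once people know whether they received the groups or are waiting.

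Part of an apparent benefit over the waitlist could then be reporting rather than change in symptoms. The alliance scores, which the plan uses as exploratory moderators or mediators, are exposed in the same way.

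**Working it through.** **1. Who the helper is.** The section that assigns the task does not define the word *facilitators*.
- Interventions, Other measures, most of Monitoring study implementation, and the facilitator random intercepts in the analysis paragraph use it for those who lead the groups.
- Assignment to interventions uses it for NGO staff who enrol participants. Ethics and dissemination uses it for staff who explain consent to every participant.

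The first reading is the more natural one, but the second is possible.

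**2. Whether the helper is blind.** Under the first reading, no: the Discussion says the therapists cannot be blinded. Under the second, recruiters' blindness ends when the intervention begins. The mid, post and follow-up assessments all come after that point under both readings. The Discussion's safeguard concerns attendance at sessions, not completion of outcomes.

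**3. Which comparison is exposed.** The primary outcome is change from baseline to post-intervention. Under Assignment to interventions, allocation is opened only after baseline. Suppose knowledge of allocation and the helper add no shift at baseline, but shifts b_M, b_I and b_W towards improvement at post-intervention (Metaverse, In-Person, Waitlist). With true mean improvements μ, the expected contrasts are:
- Metaverse − Waitlist = (μ_M − μ_W) + (b_M − b_W)
- Metaverse − In-Person = (μ_M − μ_I) + (b_M − b_I)

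If b_M and b_I are similar and b_W is near zero, the first contrast carries the whole shift and the second almost none. Neither a mixed model nor a multiplicity correction removes b.

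**4. Size.** The article gives no value for b, so only an illustration is possible.

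*The plan's own figure.* Sample size states 45 in total, with f = 0.25, power 0.95, α = 0.05, k = 3 groups and m = 4 measurements. It gives no correlation or sphericity value; I assume ρ = 0.5 and ε = 1.
- λ = N·m·f²/(1 − ρ) = 45 × 4 × 0.0625/0.5 = 22.5
- df1 = (3 − 1)(4 − 1) = 6; df2 = (45 − 3)(4 − 1) = 126
- Power is 0.955 at N = 45 and 0.939 at N = 42, so 45 reproduces as the smallest multiple of three that reaches 0.95.

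With equal allocation, 45/3 = 15 per arm.

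*Illustration.* Take 15 versus 15, no true effect, a two-sided t test at 0.05 (28 df), and a net reporting shift of b SD. The noncentrality is b × √(15/2) = 2.739b.

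| Assumed shift b (SD) | Noncentrality | Rejection probability |
|---|---|---|
| 0 | 0 | 0.050 |
| 0.1 | 0.274 | 0.058 |
| 0.2 | 0.548 | 0.083 |
| 0.3 | 0.822 | 0.125 |
| 0.5 | 1.369 | 0.262 |

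The shifts are assumptions, and the plan does not use a two-sample t test. The table shows how rejection grows with a shift of a given size; it does not give this trial's error rates.

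**5. The efficacy message against the article's own account.** Background cites evidence that support groups help refugees. Framework and rationale says it is not yet clear whether online groups do as well as traditional ones, and that evidence on metaverse delivery is at a very early stage. The Discussion presents the trial as the first test of virtual groups in this population. An efficacy statement has some backing for in-person groups, but for the Metaverse arm it anticipates the result.

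**The case against.** The strongest reply is that the article does not say the therapists are the helpers. Consent is explained to every participant by people also called facilitators, which could point to a trial-wide support role. That stands as an ambiguity. It does not remove the point, because those staff are not described as blind after the start either.

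A reader might infer that the measurement procedure differs by arm. The article does not say so: the waitlist has the same measures and schedule, and the text does not state who helps them. A reader might also infer that facilitators sit with participants or see their answers. That is not stated; help is given only on need, completion is electronic, and Interventions mentions a step-by-step survey guide.

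The efficacy information is described for participants in general and as evidence-based. The article does not say that participants are told the Metaverse groups are proven.

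Finally, unblinded self-report against a waitlist is inherent in this design, so only the increment from the help and the message is at issue. That is right, and this increment is the avoidable part. The alliance point is secondary: that measure is not taken on the waitlist and its use is exploratory.

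**Conclusion.** The point holds as a risk of bias built into a stated procedure, and it should be corrected. Under either reading of *facilitators*, no one described as blind is assigned to help with the post-baseline outcomes, and no stated safeguard covers their completion. The likely direction is towards improvement in the active arms relative to the waitlist. For Metaverse versus In-Person, a shared shift would largely cancel. The cancellation is exact only if the two shifts are equal, and different psychotherapists lead the two arms.

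The tempting stronger conclusion is that the ratings are biased, or that the false-positive rate is some particular figure above 5%. The article supports neither. It shows an opening for bias, not its occurrence, and any error rate depends on an assumed shift. The conclusion rests on the most natural reading of who assists, and on participants knowing their arm from the start of the intervention.

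**What to change.** In Data collection, management, analysis:
- State that participants complete all questionnaires alone, through their own electronic link.
- State that session leaders neither assist nor see answers, above all for the alliance items.
- Limit help to a fixed script, the same in all three arms, given by an existing research assistant who delivers no sessions and, where possible, is unaware of allocation. Participant timeline gives a research assistant a role in randomization, so that person should not be the helper.
- Name the role that is meant, so that *facilitators* no longer covers two groups of staff.
- Replace the efficacy information with neutral wording: the benefit of these groups, particularly in the Metaverse, is what the trial is testing.

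The cost is some time from research assistants already on the project and possibly slightly more item non-response. Trial status gives a recruitment start of December 20, 2023, so assessments may already have begun. If so, record the date of the change so that outcomes collected before and after it can be told apart.
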